## Abstract

**Background:**

Infants with duct dependent heart lesions often require invasive procedures during the neonatal or early infancy period. These patients remain a challenge for pediatric cardiologists, neonatologists, and intensive care unit personnel. A relevant portion of these infant suffer from respiratory, cardiac failure and may develop NEC, which leads to inadequate growth and nutrition, causing delayed or complicated cardiac surgery.

**Methods:**

This randomized control trial will recruit term infants diagnosed with a duct dependant lesion within the first 72 h of life. After obtaining written parental consent patients will be randomized to either the physician led enteral feeding or protocol-based feeding group. The intervention will continue up to 28 days of life or day of cardiosurgical treatment, whichever comes first. The primary outcomes include NEC and death related to NEC. Secondary outcomes include among others, number of interrupted feedings, growth velocity, daily protein and caloric intake, days to reach full enteral feeding and on mechanical ventilation.

**Discussion:**

Our study will be the first randomized control trial to evaluate if standard (as in healthy newborns) initiation and advancement of enteral feeding is safe, improves short term outcomes and does not increase the risk of NEC. If the studied feeding regime proves to be intact, swift implementation and advancement of enteral nutrition may become a recommendation.

**Trial registration:**

The study protocol has been approved by the local ethical board. It is registered at ClinicalTrials.gov NCT05117164.

## Introduction

### Background and rationale

Congenital heart diseases (CHD) occur with an incidence of six to nine cases per 1,000 births (1). Within this group, infants with duct dependent heart lesions often require invasive procedures during the neonatal or early infancy period. Furthermore, a relevant portion of these infants suffer from respiratory and cardiac failure as well as necrotizing enterocolitis (NEC) which leads to malnutrition and failure to thrive within the first months of life (2, 3). Inadequate growth and nutrition often lead to delayed or complicated cardiac surgery (4). NEC is a very rare condition in full-term neonates, however the risk increases by 10–100 times in patients with CHD (2). The estimated rate of NEC in infants with CHD ranges from 1.6 to 9% and mortality rates go up to 24% (5). The exact pathophysiology of NEC in babies w CHD is unknown but is likely multifactorial. Impaired mesenteric blood flow seen in infants with CHD is caused by the disruption of systemic perfusion during diastole and predisposes the infant to NEC (6, 7). McElhinney et al. have shown that episodes of low cardiac output and shock were significantly associated with NEC with an odd ratio of 6.5 (95% CI 1.8–23.5) (7). Based on a lower pulsation index observed in infants with hypoplastic left heart syndrome (HLHS), Miller et al. hypothesized that infants with HLHS may have an abnormal systemic vasculature that predisposes them to NEC (8, 9).

These patients remain a challenge for pediatric cardiologists, neonatologists, and intensive care unit personnel. As 48% of NEC develops pre-operatively, physicians are often hesitant to start feeding in infants with duct dependent CHD (10, 11). Nevertheless, there is little evidence showing that pre-operative feeds increase the risk of developing NEC, and most of the evidence comes from retrospective trials (11, 12). Current guidelines recommend that in patients with CHD enteral feeding should be initiated within the preoperative period (13). Despite published recommendations, significant differences in practice exist among centers worldwide (14). This approach contributes to poor growth in the perioperative course (15). Furthermore, adequate nutrition prior to surgery improves postoperative outcomes such as better feeding tolerance, wound healing and length of hospital stay (16).

Increasing evidence supports preoperative feeding in this group of patients despite the increased risk of NEC (5, 17–20). However, only retrospective studies are available, and the relationship between the time of enteral feeding initiation, increasing feeding volume, velocity rates and the development of NEC has not yet been documented (21, 22).

In view of the above, we have decided to perform a prospective randomized study, to evaluate whether implementation of a standard enteral nutrition protocol in patients with duct dependent CHD is equally safe in the context of NEC compared to patients fed based on the discretion of the leading physician.

## Methods and analysis

### Objectives

The aim of this study is to assess whether initiation and advancement of enteral feeding is safe, improves short term outcomes and does not increase the risk of NEC in neonates with duct dependant lesions.

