**Data collection**								
Baseline demographics	x							
VIS	x	x	x	x				
Protein and caloric intake	x	x	x	x				
days on mechanical ventilation	x	x	x	x				
CLABSI		x	x	x				

CLABSI, central line associated blood stream infection; VIS, vasoactive inotropic support score.

This study is designed as a randomized, parallel-group, superiority multi-center trial, with an 1:1 allocation and stratification by type of lesion.

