### Sample size

Studies have reported an incidence of NEC between 7–20% in babies with duct dependent congenital heart diseases, hence we chose the incidence of 18% in the control arm and 7.6% the intervention group (7, 14, 33–35). Therefore, 192 neonates should be included in each group. In total (assuming 20% lost for follow up), 384 neonates with a duct dependent heart disease should be included in the study. These calculations were performed assuming superiority *H0: P1* = *P2* vs. *H1: P1*≥*P2* with a power of 80%, a significance level of 5%. References: https://select-statistics.co.uk/calculators/sample-size-calculator-two-proprtions/ (36).

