## Discussion

Adequate nutrition is essential to improve short-and long-term outcome in newborns born with CHD. However, significant variation among units worldwide exist in introducing and advancing enteral nutrition in this group of babies. Concerns mainly relate to the risk of feeding intolerance and bowel perforation. Our study will be the first randomized control trial to evaluate if standard (as in healthy newborns) initiation and advancement of enteral feeding is safe, improves short term outcomes and does not increase the risk of NEC. If the studied feeding regime proves to be intact, swift implementation and advancement of enteral nutrition may become a recommendation.

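### The aim asks whether protocol feeding leaves NEC no more frequent, but the trial is designed, sized and analysed for superiority, with no margin or rule to support that conclusion

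*Protocol article*

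**What the plan says.** **Question and intended conclusion (protocol article).**
- The last paragraph of Background and rationale asks whether a standard feeding protocol "is equally safe in the context of NEC compared to patients fed based on the discretion of the leading physician".
- Objectives gives the aim as to "assess whether initiation and advancement of enteral feeding is safe, improves short term outcomes and does not increase the risk of NEC". The Abstract and the Discussion repeat this aim.
- The Discussion adds: "If the studied feeding regime proves to be intact, swift implementation and advancement of enteral nutrition may become a recommendation". It does not define what the regime must show to qualify.

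**Design, size and analysis.**
- Trial design: "This study is designed as a randomized, parallel-group, superiority multi-center trial".
- Sample size: "we chose the incidence of 18% in the control arm and 7.6% the intervention group", and "These calculations were performed assuming superiority". The hypotheses are written as H0: P1 = P2 against H1: P1 ≥ P2, with 80% power and a 5% significance level. The result is 192 per group, 384 in total.
- Statistical methods calls the trial a superiority study again, makes the per-protocol set primary, and plans a two-sided 95% confidence interval for the between-group difference. Intention-to-treat is a sensitivity analysis for the primary outcomes.

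The article contains no non-inferiority or equivalence hypothesis, no margin, and no rule that says what the confidence interval must show before the trial may state that NEC is not increased.

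**The concern.** Equal safety and absence of an increase are claims about the upper end of the plausible difference in NEC. A superiority test does not address them unless it succeeds. When it fails, the data may fit no difference, a modest benefit or a real excess, and the p-value does not separate these.

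The stakes follow from the article itself. It puts mortality from NEC in infants with CHD at up to 24%, and it links the result to a possible recommendation for swifter feeding. Without a rule fixed in advance, nothing prevents a non-significant difference from being reported as meeting the stated aim.

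This is not a detail that an analysis plan could supply. The article states both the objective and the hypothesis, and the two do not match.

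**Working it through.** **Inputs.** From Sample size: 18% and 7.6%, 80% power, 5% level, 20% loss, 192 per arm. From Recruitment: at least 192 valid observations per arm, so 192 is used as the evaluable number. From Statistical methods: two-sided 95% CI for the difference. The equal-rate, harm and margin scenarios below are assumptions. The 9% is the top of the range given for all CHD in Background and lies inside the 7–20% range given for duct-dependent disease in Sample size.

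**1. The plan's own figure.** With unpooled variance,
n = (1.96 + 0.8416)² × [0.18×0.82 + 0.076×0.924] / (0.18 − 0.076)² = 7.849 × 0.2178 / 0.010816 = 158.1, so 159 per arm. The pooled-variance version gives 161. Adding 20% gives 159 × 1.2 = 191 and 161 × 1.2 = 194, which bracket 192. One-sided versions do not reach it: 127 becomes 153 or 159 after allowing for loss, and 146 with continuity correction becomes 176 or 183. So 192 is a two-sided superiority size.

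**2. If the planned effect is real.** Two-sided power at 18% vs 7.6% with 192 per arm is 86.5%. A significant benefit would also establish that NEC is not increased.

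**3. If NEC is equal in both arms.** The chance of a significant benefit is about 2.5%. The half-width of the interval is 1.96 × √(2p(1−p)/n):
- p = 9%: 1.96 × √(0.1638/192) = 5.7 points. With no observed difference, 14.7% against 9% is not excluded.
- p = 18%: 1.96 × √(0.2952/192) = 7.7 points. With no observed difference, 25.7% against 18% is not excluded.

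Sample size can also be read as counting the 20% loss inside the 192. That leaves 192 × 0.8 ≈ 154 per arm, and the half-widths become 6.4 and 8.6 points.

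**4. If protocol feeding raises NEC (assumed rises).** P(non-significant) ≈ Φ(1.96 − d/SE), where SE = √([p₁(1−p₁) + p₂(1−p₂)]/192):
- 18% to 24%: SE = √(0.3300/192) = 0.0415; 0.06/0.0415 = 1.447; Φ(0.513) = 0.70.
- 9% to 13.5%: SE = √(0.1987/192) = 0.0322; 0.045/0.0322 = 1.399; Φ(0.561) = 0.71.

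**5. If the benefit is real but smaller than planned.** Superiority power at 192 per arm is 38% for 18% vs 12% and 12% for 18% vs 15%.

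**6. What a margin would deliver at 192 per arm.** With equal true rates, power = Φ(M/SE − 1.96), where SE = √(2p(1−p)/192), which is 0.0270 at 7.6% and 0.0392 at 18%.

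| Assumed margin M | Power, 7.6% in both arms | Power, 18% in both arms |
|---|---|---|
| 5 points | Φ(1.849 − 1.96) = 46% | Φ(1.275 − 1.96) = 25% |
| 10 points | Φ(3.697 − 1.96) = 96% | Φ(2.550 − 1.96) = 72% |

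For 80% power at 5 points, the evaluable number per arm is 7.849 × 2p(1−p)/0.05²: 441 at 7.6% and 927 at 18%.

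**The case against.** **The superiority label may fit part of the aim.** The aim also includes better short-term outcomes, for which superiority is the natural test. But the superiority hypothesis that was sized is on NEC, the outcome that the aim says should not increase.

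**The trial may well succeed.** A reader might infer that the likely result cannot support the conclusion. The document does not allow that forecast. On the planned rates power is about 87%, and shown superiority answers the safety question too. The gap opens only if superiority is not shown.

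**The authors do not say they would read a null result as safe.** That is correct. The Discussion is conditional, and the planned interval would display any excess. What stands is that no rule excludes that reading.

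**The written alternative looks one-directional.** A reader might infer from P1 ≥ P2 that harm is not tested. The rest of the plan is two-sided: the 192 fits a two-sided calculation, the confidence interval is two-sided, the interim boundaries are symmetric, and the DMC monitors safety. The line is a slip of notation.

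**The planning rates may have a source.** It is tempting to say that 18% and 7.6% are just values near the two ends of one incidence range. The article gives no derivation, but it cites several references, one of which is also cited for the study-group protocol. They are not available here, so no claim about the origin of the rates is made.

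**Conclusion.** The mismatch is wrong as written. The question and intended conclusion are about non-inferiority on NEC, while the design, sample size and analysis are for superiority, with no margin or decision rule. The consequence is conditional. A significant benefit would support the no-increase claim. A non-significant result would not, because it would leave an uncertainty of about 5.7 to 7.7 points either side at equal rates of 9% to 18%, and would miss the assumed rises in step 4 in about 70% of trials.

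The reading of the text is firm. The sizes rest on 192 evaluable infants per arm, normal approximations and the assumed rates.

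A reader might also infer that adding a margin costs no patients. Writing the rule costs none, but the present size would give a 5-point margin only about 25% to 46% power at equal rates.

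**What to change.** **Option A: keep superiority.** Reword the last paragraph of Background and rationale, the Objectives and the Discussion (and the matching sentence in the Abstract) so that they ask whether protocol feeding reduces NEC. Add to Statistical methods that a non-significant difference will be reported with its confidence interval and regarded as inconclusive about safety. This costs wording only and no patients. The price is a less favourable claim if superiority is not shown.

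**Option B: keep the safety claim.** Before any interim data are seen:
- Fix and justify a margin for the NEC risk difference (protocol minus control). The margins in the working are illustrations, not proposals.
- State that absence of an increase will be claimed only if the upper limit of the two-sided 95% CI lies below the margin in both the intention-to-treat and per-protocol sets.
- Test superiority from the same interval.
- State the power of the margin at 192 per arm, and re-size or soften the claim if that power is low.

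The cost is agreement on one margin and, if it is tight, more infants or an underpowered claim.

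**Under either option,** write the superiority hypothesis in Sample size as H0: P1 = P2 against H1: P1 ≠ P2, to match the 192 per arm and the two-sided interval. This changes no number.

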### Trial design

Parents of the neonates born after 36 weeks of pregnancy with duct-dependent CHD will be offered participation in the study within the first 3 days of life. After provision of oral and written information about the study, both parents will be asked to sign a written consent for their child to participate in the study (Table 1).

**Table 1 T1:** Study timetable.

**Timepoint (state unit)**	**T0**	**T1**	**T2**	**T3**	**T4**	**T5**	**T6**	**T7**
**Enrollment**								
Eligibility screen	x							
Informed consent	x							
Allocation	x							
**Interventions**								
	control group	x	x	x	x			
	study group	x	x	x	x			
**Assessments**								
feeding tolerance	x	x	x	x	x			
ECHO assessment	x	x	x	x	x			
Mesenteric and renal artery assessment	x	x	x	x	x			
Anthropometrics weight length head circumference						x	x	x
Breast feeding assessment						x	x	x
**Data collection**								
Baseline demographics	x							
VIS	x	x	x	x				
Protein and caloric intake	x	x	x	x				
days on mechanical ventilation	x	x	x	x				
CLABSI		x	x	x				

CLABSI, central line associated blood stream infection; VIS, vasoactive inotropic support score.

This study is designed as a randomized, parallel-group, superiority multi-center trial, with an 1:1 allocation and stratification by type of lesion.

### Methods: Participants, interventions, and outcomes

#### Study setting

The study will be carried out in four neonatal centers in Poland, including two neonatal departments at the Medical University of Warsaw (MUW), and one Neonatal Unit at Children's Health Memorial Institute (CHMI), and Polish Mother's Memorial Hospital (PMMH).

Departments of Neonatology at MUW are level III and IV teaching hospitals with approximately 5,000 (150 CHD) deliveries per year. Both units are referral centers for fetuses with CHD. Having access to high-risk mothers will augment recruitment. CHMI and PMMH are regional level IV hospital providing neonatal, cardiac, and surgical care for infants with CHD. A certified breastfeeding consultant is available daily on each unit.

The local feeding regimes for infants with CHD are set at the discretion of the attending doctor. However, the staff, in both units, is willing to implement new procedures to improve neonatal outcome.

#### Eligibility criteria

All parents of infants diagnosed with a duct dependant lesion and admitted to participating units will be approached by one of the research team members within the first 72 h of life (as full enteral feeding is usually reached at a minimum of 7 days of life). He or she will explain the study and obtain written consent for participating in the trail. Recruitment will take place between June 1st 2022 and June 30st 2024. After obtaining written consent for participating in the trial, the patient's medical record number (MRN) will be immediately registered on REDCap (Research Electronic Data Capture). Patients eligible for the trial must comply with all the following **at randomization**.

#### Inclusion criteria

1. Duct dependent CHD: assessment of ductus arteriosus (DA) will be done using the parasternal short axis view or suprasternal view.ductal diameter size will be measured using 2D imaging or by color Doppler at the narrowest point usually at the pulmonary end of the duct (mm).shunt direction (using pulsed Doppler) will be defined as one of the followings; left to right or right to left shunt, or bidirectional.2. Term infants.3. Parental/legal guardian consent.

#### Exclusion criteria

1. Potential contradictions to early central feeding; neonates with gastrointestinal anatomic and maxillofacial abnormalities.2. Feeding intolerance defined as vomiting bile or haemorrhagic residuals (23).3. Hemodynamic instability defined as hypotension requiring at least two inotropes for at least 72 h.4. > 50% formula based enteral feeding Studies have shown that infants with duct dependent CHD, who were fed with a predominately human milk-based diet have a lower risk of NEC.5. Birth weight <2500 g In a large multi-center cohort of patients with HLHS, El-Hassan et al. failed to show an increased risk of NEC, but outcomes were worse in the group of babies with low birth weight (24).

Optimal nutrition is crucial to improve short- and long-term outcomes in newborns with CHD. However, large, well designed randomized controlled studies are not available, hence feeding practices differ between units and physicians. Furthermore, a position statement regarding nutritional support for children with critical illnesses (including CHD) is based on studies in preterm populations (13). Given the above, selecting a physician led enteral feeding regime as a comparator is therefore justified.

Patients will be randomized to either the physician led enteral feeding (control group) or protocol-based feeding group (study group).

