#### Study group

To meet the nutritional goals, infants will receive enteral feeding based on the following protocol (14):

Minimal enteral nutrition (MEN) will begin within 72 h life at 10 to 20 mL/kg/day, breast milk/donor human milk. MEN will not be included in the caloric goals.Advancements in feeding will be set at 20–30 mL/kg/day, but not more than 10 ml per feeding portion to reach a goal of 150 ml/kg/day, but not more than 120ml/kg/day in cases of fluid restriction).The goal will be to reach an overall daily caloric intake of minimum 100 kcal/kg/d.

In both groups the interventions will continue up to 28 days of life or day of cardiosurgical treatment, whichever comes first.

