### Assignment of interventions

#### Allocation (sequence generation, concealment mechanism and implementation)

A member of the recruitment team will approach caregivers within the infant's first 72 h of life. He or she will explain the study and obtain written consent for participating in the trail. Infants who fulfill inclusion criteria will be randomized.

A study number together with the allocated treatment will be assigned by REDCap. The allocation sequence will be computer-generated. Patient's data along with the result of the allocation will be sent to statistical team. Block randomization with stratification by type of lesion (ductal dependent pulmonary, systematic, or mixing blood flow) will be implemented. Patients will be randomly assigned to standard or physician-led enteral nutrition guidelines in 1:1 ratio. To ensure allocation concealment, the randomization list will remain with the statistical team for the whole duration of the study. The block size will be variable and concealed until primary endpoint analyses.

Thus, randomization will be conducted without any influence of the principal investigators, clinicians, recruitment or follow up staff.

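### The haemodynamic exclusion asks for 72 h on two inotropes, but infants are allocated by about 72 h of life, so it can screen out practically nobody

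*Protocol article*

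**What the plan says.** All references are to the protocol article.

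- **Exclusion criteria**, item 3: "Hemodynamic instability defined as hypotension requiring at least two inotropes for at least 72 h". None of the other four exclusions is haemodynamic.
- **Eligibility criteria**, on when the criteria are judged: "Patients eligible for the trial must comply with all the following at randomization".
- **Eligibility criteria**, on recruitment: parents "will be approached by one of the research team members within the first 72 h of life". The Allocation section agrees: "A member of the recruitment team will approach caregivers within the infant's first 72 h of life". Trial design puts it in days: parents "will be offered participation in the study within the first 3 days of life".
- **Table 1** marks eligibility screen, consent and allocation at T0 only, and **Participant timeline** defines T0 as day 1 of life.
- **Study group**, on the start of the allocated intervention: "Minimal enteral nutrition (MEN) will begin within 72 h life at 10 to 20 mL/kg/day".
- **Criteria for modifying or discontinuing allocated interventions** lists abdominal signs, feeding intolerance, temperature instability, and perforation or necrotising enterocolitis (NEC). It has no haemodynamic item.
- **Background and rationale** reports from a cited study that "episodes of low cardiac output and shock were significantly associated with NEC".

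On a separate matter, Trial design describes "neonates born after 36 weeks of pregnancy", while the Inclusion criteria ask for term infants without giving a limit in weeks.

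**The concern.** An exclusion criterion works only if some candidates can meet it when it is checked. This one needs three days of treatment, and it is checked in infants who are at most about three days old.

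The investigators evidently meant to keep haemodynamically unstable infants out of a trial of standard feed advancement. If the criterion cannot be met at randomisation, a hypotensive infant already on two inotropes is eligible as the text stands and has an even chance of allocation to protocol feeding. No other eligibility or discontinuation rule in the article would catch that infant. The enrolled population would then differ from the intended one, in a trial whose primary outcome is NEC and whose stated aim includes safety.

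**Working it through.** The article gives no figure to reproduce; the check is arithmetic on its stated times.

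**Inputs**
- Threshold: at least 72 h on at least two inotropes (Exclusion criteria, item 3).
- Moment of assessment: randomisation (Eligibility criteria).
- Age at randomisation: day 1 of life by the timetable, so at most 24 h. By the approach window it could be later, up to about 72 h. Study-group feeds start within 72 h of life and can follow only from an allocation already made, so randomisation should not fall after 72 h.

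**Formula**

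Hours on two inotropes at randomisation = age at randomisation − age when the second inotrope was started.

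The criterion is met if the result is at least 72 h.

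| Age at randomisation | Start at birth | Start at 1 h | Start at 6 h | Start at 12 h |
|---|---|---|---|---|
| 24 h (T0) | 24 h | 23 h | 18 h | 12 h |
| 48 h | 48 h | 47 h | 42 h | 36 h |
| 72 h | **72 h** | 71 h | 66 h | 60 h |

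Only one cell reaches the threshold: two inotropes from the moment of birth, with randomisation at 72 h. For any randomisation before 72 h of life the criterion cannot be met at all.

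**The same check in reverse**

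Earliest age at which the criterion can be met = age at start + 72 h. A start at 6 h of age gives 6 + 72 = 78 h, and a start at 12 h gives 12 + 72 = 84 h. Both fall after the time by which study-group feeds should have begun.

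**The case against.** **The 72 h limit applies to the approach, not to randomisation.** This is correct as far as it goes. Trial design, Eligibility criteria and Allocation limit when parents are approached or offered participation, and none states a maximum age at randomisation. The T0 label also cannot be taken as a strict limit on allocation, because those same sections allow enrolment up to day 3. The objection rules out saying that the criterion can never be met. It does not rescue the criterion, because the feeding start within 72 h of life still places randomisation inside the window.

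**The 72 h may mean an expected need for support.** The text does not say so. If that was meant, sites have to guess it, and the wording still needs correcting.

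**An article condenses the full protocol.** That would answer a missing detail. Here both the criterion and the timing are stated, and they conflict.

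A reader might also draw three stronger conclusions, which the article does not support:

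- *That enrolling unstable infants biases the comparison.* Under concealed 1:1 allocation both arms receive them. The population, its risk and the precision may change, but the contrast between arms is not biased by this alone.
- *That sites will remove such infants after allocation once 72 h have passed.* No section says this. Eligibility is tied to randomisation, and infants who stop the intervention remain on study to 12 months.
- *That the odds ratio of 6.5 (95% CI 1.8–23.5) in the Background measures the damage.* It relates episodes of low cardiac output and shock to NEC in a cited study. It does not describe hypotension on two inotropes in the first 72 h of life. It shows why haemodynamic state is relevant, and no more.

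**Conclusion.** The point holds as an internal inconsistency: exclusion 3 is practically unattainable at the time the article says it is judged. It is strictly unattainable for any randomisation before 72 h of life. At 72 h it is attainable only with two inotropes from birth. As written, it screens out practically none of the infants it is meant to exclude, and they may be allocated to protocol feeding.

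The consequence concerns safety and the intended population, not the validity of the randomised contrast. Its effect on NEC counts cannot be sized, because the article does not say how many eligible infants would be hypotensive on two inotropes at randomisation.

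The conclusion rests on two readings: that the 72 h is time already elapsed, as the wording has it, and that randomisation comes before the study-group feeding start.

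The gestational-age wording is a separate, minor point. Birth after 36 weeks and term may be read as different limits, but the article does not show that sites would enrol differently because of it.

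**What to change.** Reconcile exclusion 3 with Trial design, Eligibility criteria, Table 1 and Participant timeline, Study group, and Allocation. The result should be a haemodynamic exclusion that can be assessed at the actual time of randomisation and is applied only then. Whether the duration, the timing or both should change, and what clinical threshold applies, is for the investigators to decide. As part of the same edit, the T0 label for allocation should be made consistent with the window of 72 h or 3 days.

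Separately, state one gestational-age limit in the same terms in Trial design and in the Inclusion criteria.

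The cost is a short eligibility amendment. A few infants who are eligible under the present wording may become ineligible.
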